## Outcome assessments

All outcomes will be measured at baseline, 3-, 6- and 12-months post commencement (Table 1). Participant characteristics obtained at baseline will include age, gender, work status, ethnicity, time off work due to back pain in the last month, self-reported back pain intensity at the start of recent treatment, back pain medication use in the last month, physical activity levels in the last week, and back pain treatments undertaken in the last month.

**Table 1 Tab1:**
[figure not shown]
Schedule of procedures

### Primary outcomes

The primary outcome measures are proportion of participants reporting low back pain (current and in the last 7 days) ≥ 3 out of 10 (using the numeric pain rating scale, 0 (no pain) to 10 (worst possible pain) at 3, 6 and 12 months; and pain intensity (current and in last 7 days) reported at 12 months [35].

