Cognitive behavioural therapy (CBT) is a psychosocial therapeutic method of behavioural change focussed on restructuring maladaptive beliefs and emotions as well as improving coping skills and behaviours [31]. It has been shown to be effective in improving pain, physical function, quality of life and pain catastrophizing beliefs [31–33], and is a recommended first line of treatment for chronic low back pain [11]. Additionally, combining MI with complementary treatments such as CBT, that is MI-CBT, has been shown to improve health-related outcomes such as physical activity and body composition [24]. However, to our knowledge, no previous studies have examined the potential of MI-CBT to facilitate established self-management strategies (education and exercise) for reducing back pain recurrence after an acute episode of low back pain.

This protocol paper outlines the design of a randomized controlled trial, which aims to assess the effectiveness of patient education and exercise advice facilitated by MI and CBT techniques (*Edu* + *MI-CBT*) compared to education and exercise (*Edu only*) in preventing low back pain recurrence among individuals who have recently recovered from an acute episode. The primary objectives are to examine the proportion of patients reporting pain ≥ 3 out of 10 at 3, 6 and 12 months [9] and the pain intensity reported at 12 months, between the two groups. Secondary objectives include examining changes in pain catastrophizing, fear-avoidance beliefs, pain self-efficacy, depression and anxiety, and disability, as well as monitoring ongoing treatment, medication usage and physical activity reporting. Positive findings from this trial will inform the scalable implementation of such strategies within the primary care system of New Zealand.

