### Sample size estimation

The sample size for the main trial is 166 (*n* = 83 per intervention group) based on a 1.0 ± 2.0-point difference in numeric pain rating at 12-months between groups, which is suggested to be the minimum difference to detect a clinically meaningful change. Sample size estimation (1-ß = 0.80, α = 0.05) included group x time interactions over the 3 time points and allowed for a 15% drop-out [45].

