## Statistical methods

Data will be analysed by a statistician who is blinded to group membership. The primary analyses will be by intention-to-treat for any missing data using the last-point-carried-forward method. Multiple-mediation analysis with bias-corrected bootstrapping will be used to explore how changes in participant self-report explains relationships between group (Edu + MI-CBT vs. Edu) and 12-month outcomes for back pain intensity and disability, with healthcare seeking behaviours (i.e., patient reported number of treatments and medication use) examined as potential moderators of observed effects. Statistical significance will be set at *p* ≤ 0.05.

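### Two unranked primary outcomes, spanning two to eight tests depending on the reading, share one 0.05 threshold, and nothing says which result decides the trial

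*Protocol article*

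**What the plan says.** Primary outcomes opens with a plural: "The primary outcome measures are proportion of participants reporting low back pain (current and in the last 7 days"), at a cut-off of 3 out of 10. It continues "at 3, 6 and 12 months; and pain intensity (current and in last 7 days) reported at 12 months". Recurrence is therefore primary at three visits and intensity at one, and both carry the same pair of ratings.

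The Introduction puts the two side by side as objectives: "The primary objectives are to examine the proportion of patients reporting pain ≥ 3 out of 10 at 3, 6 and 12 months", "and the pain intensity reported at 12 months, between the two groups". It ranks neither and does not mention the two ratings.

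Statistical methods has one sentence on thresholds, "Statistical significance will be set at" p ≤ 0.05. It gives no order of testing, no split of alpha and no rule on how many primaries must succeed.

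Sample size estimation rests on a "1.0 ± 2.0-point difference in numeric pain rating at 12-months between groups", with "Sample size estimation (1-ß = 0.80, α = 0.05"). Alpha is not divided, and neither the current nor the last-seven-days rating is named. The section adds that group-by-time interactions over three time points were included and that 15% drop-out was allowed for.

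**The concern.** A superiority trial needs one pre-stated condition under which it may claim success. Here the condition is open in four ways: which outcome leads, which rating is used, which visit counts, and whether one success or all are required. The title and aim point to recurrence, while the sample size points to 12-month intensity. Recurrence is also loosely defined, since a participant could reach 3 on the current rating, on the last-seven-days rating, on either or on both.

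If the answer is settled after the data are seen, the claim can rest on whichever result falls below 0.05, and the 5% error rate no longer describes the trial's main conclusion. The choice also bears on a sample size that is already fixed, because any split of alpha costs power.

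**Working it through.** **Counting the tests**

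- Eight: recurrence at 3 visits × 2 ratings = 6, plus intensity at 1 visit × 2 ratings = 2.
- Four: one rating only, so 3 + 1.
- Two: one rating and one test per outcome, so 1 + 1.

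Twelve is not a possible count, because intensity is primary at 12 months only.

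**Error rate if any single success counts, independent tests**

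1 − 0.95^k gives:
- k = 2: 0.098
- k = 4: 0.185
- k = 8: 0.337

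These are upper values. Recurrence is the same score cut at 3, so the tests are positively correlated.

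**Error rate with correlation (simulated under no effect)**

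Inputs from the protocol:
- 0–10 scale with cut-off 3
- three visits and two ratings
- 83 per arm less 15%: 83 × 0.85 = 70.6, taken as 70
- SD 2.0, reading the ± figure as an SD

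Inputs assumed, because the protocol gives none:
- correlation 0.3–0.7 between visits and 0.6–0.9 between ratings
- about 35–40% with pain of 3 or more (the Introduction cites 25–60% recurrence at one year)
- two-sided tests

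| Reading | Chance of at least one p ≤ 0.05 |
|---|---|
| Two tests (12 months, one rating) | about 0.07 (runs 0.07–0.08) |
| Four tests | 0.14–0.16 |
| Eight tests | 0.21–0.28 |

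Higher correlation gives the lower end. Carrying the last value forward, as Statistical methods plans, copies scores between visits and so pushes that way.

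**The plan's own sample size**

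For two means, n per arm = 2 × (1.960 + 0.842)² × 2.0² / 1.0² = 62.8, so 63 (64 by t-test). Dividing by 0.85 gives 75–76, against 83 stated. The group-by-time correlation is not given, so the stated method cannot be rerun. As 83 is the larger figure, this gap is not shown to be an error and does not affect the point.

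**What each decision rule would cost (12-month intensity, difference 1.0, SD 2.0)**

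| Alpha for the test | n per arm with drop-out, 80% power | Power on 70 per arm (normal approximation / t-test) |
|---|---|---|
| 0.05 (one deciding primary) | 75 | 0.84 / 0.84 |
| 0.025 (two primaries, Holm first step) | 91 | 0.76 / 0.75 |
| 0.00625 (Bonferroni over eight) | 122 | 0.59 / 0.57 |

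**Recurrence as lead**

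The protocol gives no power for it. As an illustration only, assume a fall of 15 percentage points from control rates of 60%, 45% or 40%. Power on 70 per arm is then 0.43, 0.45 and 0.47. An assumed fall from 60% to 33% would give 0.90. The answer depends on an effect that the protocol does not state.

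**The case against.** The strongest reply is that this is a condensed article and the analysis plan is not shown. Multiplicity rules are commonly left to that plan, and a general threshold of 0.05 does not say that each visit and rating gets its own unadjusted test. That stands as far as the method of adjustment goes. It does not reach the definition of the primary outcome, which the protocol itself sets, and sets with two unranked outcomes and two ratings.

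A second reply is that eight is the largest possible count. The Abstract treats the pain ratings as feeding one recurrence count, the Introduction does not split by rating, and the group-by-time remark hints at a longitudinal model rather than visit-by-visit tests. All of that is fair, and it is why the range starts at two. Even two tests exceed 5% if either may carry the claim.

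A third reply is that success might require every primary. There would then be no inflation, but the protocol does not say so and gives no power for the recurrence tests.

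Three stronger readings are tempting and not supported. A reader might infer that the trial's error rate is 34%; that needs eight independent tests and an any-one-wins rule. A reader might infer that the trial is sized on the last-seven-days rating; Sample size estimation says only "difference in numeric pain rating at 12-months between groups". And a reader might conclude that intensity must lead because the trial is sized on it; the title and aim centre on recurrence, so the choice belongs to the investigators.

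**Conclusion.** The point holds as a badly fixed primary, not as a missing adjustment method. Two unranked primary outcomes, two ratings and three visits stand under one 0.05 threshold, with no rule on what decides the trial.

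If any one success counts, the chance of a false-positive primary claim is about 7%, 14–16% or 21–28% for two, four or eight tests. The sizes depend on the assumed correlations. The direction does not: every multi-test reading tried exceeds 5%. The one exception is a rule that all primaries must succeed, which the protocol does not state. This should be settled before any unblinded look at the data.

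**What to change.** By a dated, justified amendment to the protocol and the registry entry, before any unblinded look:

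1. Name one deciding primary (one outcome, one rating, one time point), tested two-sided at 0.05.
2. Define recurrence on one stated rating.
3. Test the other outcome next, in fixed sequence, only if the first succeeds.
4. Label the remaining rating and time points as supportive.
5. State in Sample size estimation which rating the calculation refers to.

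Twelve-month intensity is the lead that the present size supports. If the investigators prefer recurrence, which matches the title and aim, they should state its assumed rates and power.

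The cost is an amendment, and fewer results that can be called primary. Keeping both outcomes primary under Holm is possible but not free: power for 12-month intensity at the first step (0.025) should then be restated as about 0.75 on 70 evaluable per arm, below the stated 0.80. Restoring 0.80 at that level would need about 91 per arm, or 182 in total against 166.

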### Secondary outcomes

#### Catastrophizing

The Pain Catastrophizing Scale is a 13-item self-report questionnaire widely used to assess pain catastrophizing, with good levels of validity, reliability, internal consistency, and precision [36].

#### Fear avoidance

The Fear-Avoidance Beliefs Questionnaire (FABQ) consists of two subscales related to work activity and physical activity, where each item is scored on an ordinal 7-point Likert-type scale [37].

#### Pain self-efficacy

The Pain Self-Efficacy Questionnaire (PSEQ) is a 10-item questionnaire that allows participants to rate their confidence from 0 (not at all confident) to 6 (completely confident) in performing activities while in pain [38].

#### Mental health

The Hospital Depression and Anxiety Score (HADS) is a commonly used self-rating scale developed to assess psychological wellbeing, particularly in the domains of anxiety and depression [39].

#### Disability

The Oswestry Disability Index (ODI) is one of the most used questionnaires for examining the impact of low back pain. It assesses perceived disability in 10 activities of daily living, with each item consisting of 6 statements which are scored from 0 (least disability) to 5 (greatest disability). It has been shown to be a valid, reliable, and responsive tool that is easy to administer in the clinical setting [40].

#### Other

Other outcomes such as treatment received, medication use for low back pain, low back pain-related work absence and physical activity levels will be collected via single-item forced choice and open answer items.

## Intervention

Both groups will have two 30-min face-to-face sessions (Session 1 and Session 2) separated by approximately 1 week. In Session 1, all participants will be provided with a ‘Navigating Pain’ booklet [41] (NZ Pain Society). ‘Navigating Pain’ is a freely available resource specifically designed by health care professionals to help people in New Zealand understand and manage their pain. Content includes sections covering Understanding Pain (i.e., knowledge and definitions), Understanding Their Personal Situation (i.e., intrapersonal factors), Healthy Lifestyle Choices (i.e., physical activity and sleep), and Living Your Life (i.e., identifying support, use of pacing). Additionally, a ‘homework book’ will be provided to all participants (Supplementary File 3). This book covers five scenarios based on the sections of ‘Navigating Pain’. These include: (1) Understanding Pain, (2) Sleep, (3) Exercise, (4) Back Pain and You, and (5) Giving Advice to Future You. They are designed to explore thoughts, encourage self-reflection, and plan strategies for future pain in accordance with principles of CBT for pain presentations. In Session 2, all participants will be provided with an exercise programme for back pain. Thereafter, a further three sessions will be provided (either face-to-face or via telephone) in between weeks 4–10, and these will be used to follow up on the exercise and reiterate key messages from the education booklet as well as discuss relapse prevention strategies.

The *Edu* + *MI-CBT* intervention will begin with a face-to-face session (Session 1) which will allow participants to share their pre-back pain activities, motivations for trial participation, and prior experiences with back pain and recovery. MI techniques will be employed to develop rapport, explore motivations and barriers to self-management of pain, as well as understanding participants' unique perspectives. The homework book will also be introduced to participants in Session 1 emphasizing its role in comprehending pain beliefs, sleep habits, physical activity, and action planning (reinforcing CBT strategies). Participants' ambivalence and concerns regarding use of the homework book will be addressed collaboratively, eliciting the client’s perceived benefits of working with the book in addition to engaging in flexible goal setting for outcomes from trial participation in line with MI protocols. Session 2, in addition to the exercise program, participants will review the homework to assist in the understanding pain and physical activity scenarios. MI-CBT techniques such as open-ended questions, affirmations, reflections, and summarising, will be used to explore pain beliefs around the core message that pain does not always equate to damage. The multifaceted nature of pain perception will be explored, acknowledging that various factors, including life stressors, past experiences, and expectations, can influence pain perception. In line with an MI approach, participants' personal insights and beliefs about pain will be elicited, and discussions revolve around how this understanding impacts their own pain perception and management. Participants' thoughts on the importance of physical activity for preventing future back pain are explored, and personalized exercise advice will be offered based on their preferences and history. This approach will emphasize individualized exercise recommendations, highlighting the effectiveness of various exercise types while allowing participants to lead the discussion towards the exercise solution that suits them best. The MI-CBT follow-up sessions will offer ongoing guidance on 'Navigating Pain,' individualized support, and reinforcement of engagement in physical activity. In session 3, participants' perceptions of sleep quality will be explored. This includes addressing how participants might feel in the morning after waking, reasons for sleep changes, capacity to sleep confidence levels, and strategies for improving sleep quality (e.g., sleep hygiene). Collaborative goal setting will be used to develop a bedtime routine and improve sleep quality, considering individual preferences and readiness for change. In session 4, participant’s individual beliefs about the cause and improvement of their back pain will be explored, with a non-judgmental and empathetic approach that aligns with the spirit of MI to understand their perspective. The focus is on eliciting their beliefs and exploring any ambivalence regarding the potential factors contributing to their back pain and its improvement. Finally, in Session 5, participants will be encouraged to reflect on the scenario where they provide advice to their future selves about dealing with back pain. This will focus on translating advice into a personalized action plan, setting clear goals, and emphasizing self-efficacy for managing and preventing future back pain episodes.

In the *Edu-only* intervention, standard essential resource materials are provided, in commonly used directive manner that will actively refrain from offering individualized support or incorporating MI-CBT elements. Specifically, research clinicians will actively listen, express interest, and provide undivided attention to participants without employing specific MI-CBT-based support or tailored pain education advice. Instead, participants will be directed to utilize the 'Navigating Pain' booklet in its standard form or receive answers directly quoted from its content, without customization or additional guidance. Furthermore, they will be advised to adhere to the exercise program. This approach distinguishes the *Edu-only* intervention by its emphasis on question–answer driven discussions and the deliberate absence of MI-CBT elements, ensuring a clear differentiation from the MI-CBT intervention group.

The two researchers undertaking data collection will undergo training on MI-CBT practises, involving the equivalent of a 2-day initial training by a Motivational Interviewing Network of Trainers (MINT) qualified trainer, and thereafter 2 sessions of individualised training. The trial will be conducted at one site, and adherence to protocol will be monitored by the larger research team.

### Intervention fidelity

Proficiency in the delivery of MI will be assessed using the Motivational Interviewing Treatment Integrity scale 4.2.1 (MITI 4.2.1) [42], and the Behaviour Change Counselling Index (BCCI) will be used to assess researcher competence in eliciting participants thoughts and cognitions, addressing the CBT strategies of the intervention [43]. Twenty random intervention sessions (10 from each group) will be audio-recorded for analysis of intervention fidelity at various time points during the trial, including confirmation that MI-CBT techniques were not used in the *Edu-only* group. A third-party assessor trained in the use of the MITI and BCCI, and not otherwise associated with the study, will review, and score the interactions.

Participants are permitted to seek any treatment needed during the study, and details of treatment for low back pain will be collected. The allocated intervention will be discontinued if the participant chooses to withdraw for any reason, can no longer physically complete the intervention, and/or meets the exclusion criteria during the trial. In accordance with the Health and Disability Ethics Committee (HDEC) standard, any risk to the participants will be mitigated, for example, for any scores > 10 on the HADS, a registered psychologist from the research team will contact the participant to provide further guidance and support. If the research team have any further concerns, this will be raised within 24 h of notification to the Director of the community clinic, and further support can be provided through the normal clinical operational protocols [44].

### Sample size estimation

The sample size for the main trial is 166 (*n* = 83 per intervention group) based on a 1.0 ± 2.0-point difference in numeric pain rating at 12-months between groups, which is suggested to be the minimum difference to detect a clinically meaningful change. Sample size estimation (1-ß = 0.80, α = 0.05) included group x time interactions over the 3 time points and allowed for a 15% drop-out [45].

### Ethics and management

A detailed description of the data to be collected at each time point (3-, 6- and 12-months) is presented in Table 1. All participants will be informed of, and provide consent for, the collection and use of their data for the purposes of this study, and for any mandatory secondary uses. Participants’ privacy and confidentiality will be respected through the protection of their data. The researchers will comply with legal and regulatory requirements regarding the privacy and confidentiality of participants’ data. Written consent forms, which will contain identifiable data, will be stored in a separate, secure location from the de-identified health information, accessible only to members of the research team. All paper-based documentation will be stored in a secure cabinet at the research site, and electronic documentation will be stored on a password-protected cloud-based server. All documents and data will be shredded or deleted 10 years after the study has been completed. The study has been approved by the Ministry of Health (New Zealand) Health and Disability Ethics Committee (HDEC reference: 2023 EXP 16691).

## Statistical methods

Data will be analysed by a statistician who is blinded to group membership. The primary analyses will be by intention-to-treat for any missing data using the last-point-carried-forward method. Multiple-mediation analysis with bias-corrected bootstrapping will be used to explore how changes in participant self-report explains relationships between group (Edu + MI-CBT vs. Edu) and 12-month outcomes for back pain intensity and disability, with healthcare seeking behaviours (i.e., patient reported number of treatments and medication use) examined as potential moderators of observed effects. Statistical significance will be set at *p* ≤ 0.05.

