### Participant eligibility and recruitment

Participants will be eligible to participate in the study if they are 18 years and older and have recovered (defined as ≥ 7 consecutive days with pain ≤ 2 on a 0–10 numeric pain rating scale) from a recent (i.e., pain onset within last 3-months) episode of acute non-specific low back pain (defined as pain in the area between the 12th rib and buttock crease not attributed to a specific diagnosis) and they have received treatment for this at the New Zealand College of Chiropractic Clinic.

Participants will be excluded from the study if they have any specific low back pain diagnosis (e.g., discitis, malignancy, axial spondyloarthropathy); radiating or referred pain past the buttock; previous spinal surgery; have had any back pain in the last year prior to the most recent episode that has required them to seek treatment from an allied health professional or take pain relieving medication; diagnosed with any co-morbidity that prevents participation in exercise; inadequate English language that prevents completion of outcome measure assessment or engagement in the intervention.

The study will be conducted at the community clinic of the New Zealand (NZ) Chiropractic College in Auckland, New Zealand. Participants are invited to participate in the study by Chiropractors and administrative staff at the community clinic, after completion of their low back pain treatment. Potential participants will be screened telephonically for eligibility prior to inclusion. The researchers will discuss the trial protocol and provide the participant information sheet to eligible participants (Supplementary File 2). Consent will be taken by a researcher/s trained in Good Clinical Practice (GCP). Participants will be given the opportunity to provide consent in-person, electronically, or by mail (Supplementary File 2).

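### Carrying the last value forward scores nearly everyone lost before month 3 as recurrence-free, because entry requires pain of 2 or less and recurrence is pain of 3 or more

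*Protocol article*

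**What the plan says.** The missing-data rule is in the Statistical methods section of the Protocol article: "The primary analyses will be by intention-to-treat for any missing data using the last-point-carried-forward method". That section names no other method.

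Four other statements decide what the rule does here:

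- **Entry** (Participant eligibility and recruitment): a participant must have "recovered (defined as ≥ 7 consecutive days with pain ≤ 2 on a 0–10 numeric pain rating scale".
- **Binary primary outcome** (Primary outcomes), assessed at months 3, 6 and 12: "The primary outcome measures are proportion of participants reporting low back pain (current and in the last 7 days) ≥ 3 out of 10".
- **Continuous primary outcome** (same section): "pain intensity (current and in last 7 days) reported at 12 months".
- **Visits** (Outcome assessments): "All outcomes will be measured at baseline, 3-, 6- and 12-months post commencement". For a participant with no follow-up visit, the last available point is therefore the baseline value.

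Sample size estimation plans 166 participants, 83 per arm, and allows for 15% drop-out. The Introduction puts one-year recurrence at 25 to 60%.

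**The concern.** Carry-forward assumes that a participant's pain stays where it was last seen. In this trial the first observed value lies below the event threshold because of the entry criterion. For a participant lost before month 3 the rule does not estimate an unknown outcome. It records the favourable one, at all three visits, in a condition that the article itself says often returns. The same low value becomes the 12-month pain score.

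Two things are at stake. If both arms lose the same share early, a real difference in recurrence is diluted. If one arm loses more, that arm gains extra recurrence-free participants and can look better when the treatment does nothing. Both primary outcomes are exposed.

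**Working it through.** **Plan's own figures.** The article gives no figure for the effect of the missing-data rule. The one that bears on it is planned loss: 166 × 0.15 = 24.9, about 25 participants (83 × 0.15 = 12.45 per arm). The sample size itself is not at issue here.

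**Step 1: who is affected, by time of loss.**

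| Last visit attended | Value carried | Recurrence status recorded afterwards |
|---|---|---|
| Baseline | 2 or less for nearly all | Not recurred at 3, 6 and 12 months |
| 3 months | 3-month score | Whatever it was at 3 months, possibly recurred |
| 6 months | 6-month score | Whatever it was at 6 months, possibly recurred |

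Only the first row has a direction fixed by the design.

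**Step 2: recorded recurrence rate.** Let p be the true rate and e the share with no post-baseline visit. Assume that those lost would have recurred at the same rate and that there is no later loss. Each early loss counts as 0, so the recorded rate is p × (1 − e). The values of p span the Introduction's range. The values of e are assumptions, with 15% the upper bound at the planned loss.

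| True p | e = 5% | e = 10% | e = 15% |
|---|---|---|---|
| 25% | 23.8% | 22.5% | 21.3% |
| 40% | 38.0% | 36.0% | 34.0% |
| 60% | 57.0% | 54.0% | 51.0% |

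**Step 3: equal early loss.** The risk difference is multiplied by (1 − e), so at e = 15% it shrinks by 15%. As an illustration with assumed rates of 40% and 22%: 0.85 × 40% = 34.0% and 0.85 × 22% = 18.7%, so 18.0 points become 15.3. Power for that contrast (normal approximation, two-sided 5%) is about 71% with complete data (83 per arm), 64% with completers only (83 × 0.85 = 70.55 per arm) and 61% under carry-forward.

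**Step 4: unequal early loss, no true effect.** The false difference is p × (e₂ − e₁). Type I error comes from a two-sided pooled normal test with 83 per arm. The assumed split is 10% versus 20%, which averages the planned 15%.

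| True p | Recorded rates | False benefit | Type I error |
|---|---|---|---|
| 25% | 22.5% vs 20.0% | 2.5 points | 6.8% |
| 40% | 36.0% vs 32.0% | 4.0 points | 8.5% |
| 60% | 54.0% vs 48.0% | 6.0 points | 12.1% |

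For p = 40%: the mean recorded rate is 0.34, the standard error is √(0.34 × 0.66 × 2/83) = 0.0735, and the shift is 0.04/0.0735 = 0.54 standard errors. The rejection probability is 1 − Φ(1.96 − 0.54) + Φ(−1.96 − 0.54), about 0.085.

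**Step 5: pain intensity.** With no true effect and the same 10% versus 20% split, the false difference is 0.10 × (12-month mean − baseline mean). The article gives neither mean. If the gap is 0.5, 1.5 or 3.0 points, the false difference is 0.05, 0.15 or 0.30 points, against the 1.0-point difference in Sample size estimation.

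**The case against.** The strongest reply concerns scope and size, and much of it stands.

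- **Direction.** A reader might infer that the rule biases both primary outcomes towards no recurrence for every drop-out. The documents do not support that. The outcome is pain at the visit and in the preceding 7 days, not cumulative recurrence. Someone in a flare at 3 months and then lost is scored as recurred at 6 and 12 months even if they have recovered.
- **Number affected.** A reader might take about 25 participants as the expected number miscoded. That is the whole planned loss, placed before month 3. The article gives no timing, so it is an upper bound at that level of loss.
- **Rates.** The 40% and 22% are assumptions. The 25 to 60% range is recurrence at one year, which is not the same quantity as pain in a 7-day window. A 45% reduction from 40% gives the 22%, but the Introduction credits that figure, as a maximum, to education and exercise, which both arms receive.
- **Imbalance.** Nothing in the article predicts unequal loss. Both arms have five 30-minute sessions and the same materials, and participants are blinded to the method of delivery. With equal loss the cost is modest: 61% power against 64% for completers.
- **Discontinuation.** The intervention stops if a participant withdraws, cannot complete it "and/or meets the exclusion criteria during the trial". A reader might infer that these people leave the trial carrying a recovered score. The text stops the allocated intervention and does not say that follow-up ends.
- **Baseline value.** "Potential participants will be screened telephonically for eligibility prior to inclusion", while baseline measures come at the first session, so a few could score 3 or more by then.

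None of this rescues the rule for people with no follow-up visit. Nor is this detail left to a fuller document: the article states the rule and applies it to the primary analyses.

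**Conclusion.** The point holds for participants with no post-baseline visit. For nearly all of them, carry-forward combined with the entry criterion fixes the binary outcome as not recurred at every visit and puts the 12-month pain score near its floor. For those lost after month 3 or month 6 the bias may go either way.

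Under the upper-bound assumption that all 15% is lost before month 3, recorded rates are 0.85 of the true ones and an equal-loss risk difference shrinks by 15%; the effect is smaller if some loss is later. Under an assumed early loss of 10% versus 20% and no true effect, the arm losing more gains 2.5 to 6.0 points, with type I error of about 7% to 12%. These figures show what the rule can do. They do not forecast the trial's drop-out. The case for change rests on the mechanism, which follows from the article's own statements, and on the low cost of a better method.

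**What to change.** Replace last-point-carried-forward as the primary method, before the data are analysed.

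- **Pain intensity:** a baseline-adjusted mixed model for repeated measures on the 3-, 6- and 12-month scores, with the 12-month contrast as the primary estimate.
- **Recurrence:** a mixed logistic model, or multiple imputation that includes arm, baseline pain and earlier pain scores.
- **Sensitivity analyses:** keep carry-forward, and add missing scored as recurred. The second is as extreme in the other direction, so for early losses the two show how far the result depends on what is assumed.

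The cost is a change of wording and a little more analysis work, with no extra participants or visits. The new primary methods rely on data being missing at random given what was observed, which cannot be verified; the sensitivity analyses address this.
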